### 4.2. Inclusion criteria

In order to be eligible to participate in this study, a subject must meet all of the following criteria:

#### 4.2.1. Vestibular

##### **Symptoms**

- Chronic vestibular syndrome being presented by disabling symptoms of postural imbalance and/or impaired image stabilization (e.g. oscillopsia)

##### **VOR function**

- Reduced or absent bilateral VOR function based on at least one of the tests below meeting criteria A, with the other tests meeting criteria B:

Table 5. VOR function inclusion criteria

| VOR function test                                                                                                                                                                                  | Criteria A                                                              | Criteria B                        |
|----------------------------------------------------------------------------------------------------------------------------------------------------------------------------------------------------|-------------------------------------------------------------------------|-----------------------------------|
| Caloric response                                                                                                                                                                       | Each side $\leq 6^\circ/\text{sec}$                                     | Each side $< 10^\circ/\text{sec}$ |
| vHIT gain                                                                                                                                                                                          | Bilateral horizontal SCC $\leq 0.6$
1 Bilateral vertical SCC $< 0.7$ | 2 Bilateral SCC $< 0.7$           |
| Rotatory swing                                                                                                                                                                         | Gain $\leq 0.1$                                                         | Gain $\leq 0.2$                   |
|  Sum of bithermal (30° and 44°) maximum peak slow-phase velocity
 Horizontal VOR function with sinusoidal stimulation on a rotatory chair at 0.1 Hz with Vmax = 50°/sec |                                                                         |                                   |

**BV etiology**

- Onset of bilateral vestibular loss after the age of 2
- Vestibular dysfunction from a peripheral origin or idiopathic BV
- Patent vestibular end-organ (judged by CT)
- Vestibular function and symptoms have not recovered beyond inclusion criteria within 6 months from onset of symptoms including a 3 month rehabilitation program off vestibular suppressant medications

**4.2.2. Auditory**

- Meeting CI-candidacy in ear to implant with CVI
- Agreed to receive a MED-EL CVI implant with MED-EL sound processor

**4.2.3. General**

- Capacitated adults  $\geq 18$  years
- Proficient speaker of the Dutch language
- No contra-indications for CVI surgery
- Active participation in the trial related procedures such as regular testing, the VI fitting period, the baseline testing day and three weeks of intensive VI rehabilitation and testing in the study center (MUMC+) including an exercise regimen
- Agreed not to swim or to use or operate vehicles, heavy machinery, powered tools or other devices that could pose a threat to the participant, to others, or to property throughout the period of VI activation and until at least 1 day after VI deactivation

Remark: Patients who qualify to receive a regular CI as part of standard clinical care will have a preferential position to be included in the trial.

**4.3. Exclusion criteria**

A potential subject who meets any of the following criteria will be excluded from participation in this study:

**4.3.1. Vestibular/auditory**

- Signs of central vestibular/cochlear dysfunction or structural vestibular/cochlear nerve pathology (judged by physical examination / MRI)
- Clear signs of structural nerve pathology or indications of improperly functioning vestibular/cochlear nerves
- Requirement for electric-acoustic activation of the CI part (e.g. "hybrid" processor) prior to completion of the prolonged VI stimulation period
- Having received a cochlear implant earlier on the side to implant (e.g. explantation/reimplantation)
- Having received a cochlear implant from another brand than MED-EL in the other ear (e.g. bilateral implantation with different brands is not supported)
- Unwillingness to stop the use of antihistamines which might suppress VOR responses (e.g. cinnarizine) in the period of 1 month before until after each measurement point.

#### 4.3.2. General

- Pre-lingual onset of bilateral profound deafness (< 4 years of age)
- Active participation in another prospective clinical trial
- Pregnancy or having plans to become pregnant at the time of imaging or during the VI trial
- Orthopedic, ocular, neurologic or other non-vestibular pathologic conditions of sufficient severity to confound vestibular function tests used in the study
- Current psychological or psychiatric disorders that could significantly interfere with the use or evaluation of VI stimulation
- Physical or non-physical contraindications for MRI or CT imaging prior to surgery
- Making chronic use of psychiatric medication which suppresses VOR responses (e.g. SSRI's, benzodiazepines)
- Significant dental problems which prohibit the stable use of a 'bite bar' (used as calibration reference for the gyroscope functionality of the CVI).
- Any medical condition, judged by the research team, that is likely to interfere with a study candidate's participation in the study

#### 4.4. Sample size calculation

The main outcome parameter of the trial will be DVA (e.g. visual acuity while walking on a treadmill). Regarding the first primary objective (e.g. efficacy of prolonged VI stimulation), a comparison will be made between the condition with the CVI active and the condition with the VI-part inactive (whilst the CI remains active). Visual acuity (VA) can be expressed in several different units. However, for data analysis it is important to use the logarithm of the minimum angle of resolution (logMAR), since this unit scales linearly with the geometric progression of the visual acuity chart .

Data from previous measurements on the influence of the VI on DVA was used for the sample size calculation . Although this data is obtained with a different version of the VI (which a.o. did not allow simultaneous VI and CI stimulation), it is the closest analog available to approximate the results of this trial. To account for the between-patient difference in VA, the data from the previous experiment, expressed in logMAR, were normalized to the static VA measured for each patient. This yields mean logMAR values of 0.065 (SD 0.061) and 0.205 (SD 0.066) for VI active and VI inactive, respectively. Since the size of the dataset is too small to establish whether or not the data is normally distributed, the sample size will be calculated for a two-sided Wilcoxon signed-rank test. Significance level (alpha) is set at 0.05 and power is set at 0.80 . Both effect size and minimal sample size were calculated with G\*Power 3.1.9.7 . Effect size was determined to be 2.20, which resulted in a minimal sample size of 5.

Given the available resources (finances and available implants) and to give this statistical background a safety margin, this trial will aim to include a minimum of 8 patients, with a maximum of 13 patients. If a patient drops out of the trial after implantation, they will not be replaced due to the limited amount of implants that are available. By including at least 8 patients, we will have a safety margin for potential patient drop-outs which will ensure that we will still have enough data to prove a statistically significant change in DVA. By including more patients, we might gain more insight in the role of etiology on stimulation efficacy and interindividual differences in stimulation responses since this still small but

unique and significant population of VI recipients will pave the way towards clinical indications in the future

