### 8.5. Replacement of individual subjects after withdrawal

Due to the limited number of implantable devices available, patients will not be replaced if withdrawal occurs after implantation. However, the possibility of a drop-out has been accounted for in the sample size calculation.

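### The stated minimum of 5 patients cannot give p < 0.05 in an exact two-sided Wilcoxon signed-rank test; at the stated effect size the minimum is 6 evaluable pairs

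*Protocol*

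**What the plan says.** Section 4.4 takes DVA in logMAR, normalised to static acuity, from an earlier experiment: "This yields mean logMAR values of 0.065 (SD 0.061) and 0.205 (SD 0.066) for VI active and VI inactive, respectively". Because that dataset is too small to judge normality, "the sample size will be calculated for a two-sided Wilcoxon signed-rank test". The operating characteristics follow: "Significance level (alpha) is set at 0.05 and power is set at 0.80". The result is: "Effect size was determined to be 2.20, which resulted in a minimal sample size of 5".

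The section then sets enrolment: "this trial will aim to include a minimum of 8 patients, with a maximum of 13 patients". It ties the excess over the minimum to drop-out. Of enrolling 8 or more it says: "we will have a safety margin for potential patient drop-outs which will ensure that we will still have enough data to prove". What is to be proved there is statistical significance on DVA. Patients lost after implantation are not replaced, and section 8.5 adds that "the possibility of a drop-out has been accounted for in the sample size calculation". Section 10.1 names the same test for the main VI-OFF versus VI-ON comparison.

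**The concern.** The signed-rank statistic on a handful of pairs takes few values, so its p-value has a floor that depends only on the number of pairs. If that floor lies above 0.05 at the stated minimum, the minimum cannot meet the stated alpha and power, however large the effect.

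The figure matters because the protocol's assurance about drop-out rests on it. The implants are limited in number and losses after implantation are not made good. A reader who takes 5 as the number that must remain would believe that the primary comparison can still succeed at a count where it cannot.

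**Working it through.** **Inputs (section 4.4).** Means 0.065 and 0.205, so the difference is 0.140; SDs 0.061 and 0.066; two-sided alpha 0.05; power 0.80; effect size 2.20; minimum 5; planned enrolment 8 to 13. The within-patient correlation r is not reported and is treated below as an assumption. The checks also assume normally distributed differences with no ties or zeros.

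**1. Reproducing the effect size.** For paired data, SD of differences = √(0.061² + 0.066² − 2r × 0.061 × 0.066) = √(0.008077 − 0.008052r), and dz = 0.140 / SD of differences.

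- r = 0: SD 0.0899, dz 1.56
- r = 0.25: SD 0.0779, dz 1.80
- r = 0.5: SD 0.0636, dz 2.20
- r = 0.75: SD 0.0451, dz 3.10

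So r = 0.5 reproduces 2.20. Dividing by the pooled SD also does: √(0.008077/2) = 0.0635, and 0.140/0.0635 = 2.20. The text does not say which route was taken.

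**2. Reproducing the minimum of 5.** The asymptotic-relative-efficiency approximation replaces n by n × 3/π in the noncentral t calculation for a paired t-test.

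- n = 4: effective n 3.82, noncentrality 2.20 × √3.82 = 4.30, power 0.784
- n = 5: effective n 4.77, noncentrality 2.20 × √4.77 = 4.81, power 0.932

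The first n with power of at least 0.80 is 5, as stated.

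**3. Can 5 pairs reach p < 0.05?** The smallest exact two-sided p is 2/2ⁿ:

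- n = 5: 2/32 = 0.0625
- n = 6: 2/64 = 0.03125
- n = 7: 2/128 = 0.0156
- n = 8: 2/256 = 0.0078

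At n = 5 no outcome reaches 0.05. For the normal approximation at n = 5, the statistic has mean 5 × 6/4 = 7.5 and SD √(5 × 6 × 11/24) = 3.71. When all five improve, the continuity-corrected z is 7.0/3.71 = 1.89 (p = 0.059). The uncorrected z is 7.5/3.71 = 2.02 (p = 0.043).

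**4. Power of the exact test.** At n = 6 the test rejects only when all six differences share one sign. For dz = 2.20 the probability of this is Φ(2.20)⁶ = 0.919. The other values at dz 2.20 and 1.56 come from 400,000 simulated datasets per cell, using the exact critical values.

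| Assumed r (dz) | n = 5 | n = 6 | n = 7 | n = 8 |
|---|---|---|---|---|
| 0.5 (2.20) | 0% | 91.9% | 99.4% | 99.8% |
| 0 (1.56) | 0% | 69.1% | 90.2% | 93.6% |

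At r = 0.25, Φ(1.80)⁶ gives 80% at n = 6. At r = 0.75, Φ(3.10)⁶ gives 99%. The exact minimum is therefore 6 at the stated effect size, 6 at r = 0.25 or 0.75, and 7 at r = 0.

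**The case against.** The strongest reply is that nobody plans to analyse 5 patients. Enrolment is 8 to 13, section 13.1.9 bases its expectation of significance on 8, and exact power at 8 is 94% to 99.8% for r from 0 to 0.5. This stands. A reader might infer from the 0% that the trial is underpowered, and the numbers do not support that. The defect bites only if 5 or fewer evaluable pairs remain.

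A second reply is that section 10.1 does not fix the version of the test, and the uncorrected asymptotic p at 5 pairs is 0.043. The 0% does indeed apply to the exact and continuity-corrected versions only. But the uncorrected version rejects where the true null probability is 0.0625, so it does not honour the stated alpha and does not rescue the 5.

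Three stronger readings are tempting and should not be made.

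- **That 2.20 is not a valid paired effect size.** It is valid if r = 0.5. The document cannot show whether that correlation was estimated, assumed or bypassed; it can only be said to be unreported.
- **That the protocol promises a margin of three.** Three is 8 − 5, but no section gives a number. Section 8.5 stays true as worded, because 6 still leaves a margin of two from 8.
- **That patients without benefit are withdrawn and so erode the sample.** Section 8.4 withdraws from regular trial activities only those in whom, after repeated fitting attempts, none of the three vestibular electrodes elicits a response. It otherwise leans towards keeping patients in, and section 10.1 specifies intention-to-treat. The documents give no basis for saying how likely a fall to 5 is.

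**Conclusion.** The point holds, at moderate severity: a stated figure is wrong and the design is unaffected. The protocol's software result was not miscalculated. A continuous approximation was accepted at a sample size where the test is too discrete for it.

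The size of the correction is one patient at the stated effect size: a minimum of 6 rather than 5. The assurance of a significant result from 8 enrolled patients is conditional. At effect size 2.20 it covers at most two losses, and at r = 0 only one, if 80% power is to be kept. Even with 6 pairs left, a single patient who changes in the wrong direction removes significance.

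That 5 is unattainable under the exact test depends on no assumption about effect or correlation. The minimum of 6 rests on the stated 2.20 and on normal differences without ties or zeros.

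**What to change.** In section 4.4:

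- Restate the minimum as 6 evaluable pairs for the exact two-sided signed-rank test at effect size 2.20.
- Report the within-patient correlation or the SD of the paired differences behind 2.20. If neither is available, show the range: dz 1.56 (minimum 7) at r = 0, 2.20 (minimum 6) at r = 0.5, and 3.10 (minimum 6) at r = 0.75.
- Say that the assurance of a significant result with 8 patients holds only while at least 6 evaluable pairs remain, that is, with at most two losses from 8 at effect size 2.20.

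Section 8.5 can stay as worded if it is read against, or refers to, the revised 4.4. The cost is a few sentences and a slightly less comfortable drop-out statement. Enrolment, the primary test and the 8 to 13 range do not change.

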## 5. TREATMENT OF SUBJECTS

### 5.1. Investigational product/treatment

To provide prolonged simultaneous stimulation of both the vestibular organ and hearing organ a research device will be used: the CVI, which is presented in Figure 5. A more detailed description of the CVI can be found in section D of the standard research file (the IMDD). The basis of the CVI is a standard CI and its operating principles are the same: transferring information to the brain by means of electrical stimulation of sensory nerves. However, instead of only stimulating the auditory nerves in the cochlea, the CVI will also stimulate the nerves of the SCCs in the vestibular system. The CVI consists of two units: the implant and the external processor.

#### 5.1.1. *The implant*

The basis of the CVI implant is a MED-EL CI implant. The implant consists of a coil for receiving radio frequency signals from the external processor, a magnet to allow for attachment of the external sending coil of the processor unit to the subcutaneous receiving coil of the implant and an array of 12 electrodes. In the normal CI implant these electrodes are arranged along one branch, designed to all be inserted into the cochlea. In the CVI implant, the three most basal electrodes are separated from the main electrode branch into three individual branches. These three individual branches are designed to be inserted into the SCCs to allow for stimulation of the vestibular system. The remaining 9 electrodes make up the cochlear array, designed to be inserted in the cochlea, analogous to a regular CI. Reallocating the

electrodes within the vestibulocochlear organ offers the opportunity to stimulate the vestibular nerves, while maintaining CI functionality in order to restore hearing.

Due to the similarities between the CVI and the cochlear implant, the CVI can be used in combination with a regular CI processor. In this case, the CI processor is programmed to only stimulate the 9 electrodes which are inserted into the cochlea, with the three vestibular electrodes turned off. This makes the CVI implant perform like a regular CI, without stimulation of the vestibular nerves. Outside of the VI testing periods, the patients who receive a CVI will be able to use the implant as a regular CI driven by a regular CI processor (described in chapter 7). During the VI testing periods, the patients will use the experimental CVI processor described in 5.1.2.

With the redesign of a standard CI implant into the CVI implant, the amount of intracochlear electrodes is reduced from 12 to 9, and the overall length of the cochlear array is reduced from 31 mm to 24 mm. It is difficult to make definitive statements on what influence these design changes might have on the CI performance of the CVI. Among the major CI manufacturers, there is no consensus on what the optimal electrode design is. Due to the differences in design philosophies between the companies, large differences in cochlear array designs exist. These designs include both straight and pre-curved arrays ranging in length from 18 to 31 mm containing between 12 and 22 electrodes . These different designs yield large variations in the amount of stimulating electrodes, electrode spacing, angular insertion depth, cochlear coverage and frequency-to-place matching. However, a comparison study between the different brands yields only a 14% difference in overall performance , even though individually all these aspects have been shown to influence hearing outcomes.

Looking at the number of stimulating electrodes, research gives some broad outlines concerning its relationship with CI performance, although making comparisons is difficult due to large interpatient variability . Based on theoretical knowledge of cochlear anatomy and signal transduction, increasing the amount of stimulating contacts in the cochlea should increase CI performance. However, this correlation does not appear to be so straight-forward. When looking at normal-hearing subjects, Shannon et al.  showed that speech recognition was mainly influenced by temporal information rather than spectral information. They demonstrated that, as long as enough temporal information was maintained in the signal, only a reduction of spectral information into 3 or less distinct spectral bands resulted in reduced speech discrimination. In other words: 4 electrodes distributed throughout the cochlea could theoretically be sufficient for near-normal speech discrimination. Looking at CI recipients, research into the number of active cochlear electrodes necessary for speech discrimination indicates that speech perception improves with an increasing number of electrodes, but plateaus around 8 electrodes , most likely due to current spread and increasing overlap in spectral stimulation. Along this line, Riss et al.  concluded that 4 electrodes are sufficient for simple listening tasks while more difficult tasks required up to about 8 electrodes, regardless of the used signal-processing strategy.

When reviewing the influence of cochlear array length on CI performance, conflicting results inhibit the drawing of definitive conclusions. Based on theoretical knowledge, a longer cochlear array should perform better due to the increase in frequency-to-place match and inter-electrode angular contact spacing . This is substantiated by several studies, showing that utilizing the longest electrode possible which will fit

in a patient's cochlea results in the best performance . However, contradictory studies found that by further inserting electrode arrays into the cochlea, and thereby increasing the frequency-to-place match and inter-electrode angular contact-spacing, no difference was observed in CI performance . Deep insertion of a cochlear array has even been associated with reduced performance due to damage to the structures inside the cochlea . When looking at the development of cochlear array designs over the past years, CI manufacturers seem to converge to a similar array length of between 20 and 25 mm, rather than making arrays which are as long as possible, compromising between cochlear coverage and causing structural damage .

The above-mentioned body of research is not capable of conclusively substantiating any claims regarding the influence of the redesigned CVI cochlear array on CI performance. Both the amount of electrodes and the array length are within industry standards and supported by literature. Preliminary results of research performed within our own consortium is indicating that there is no difference in performance between a regular CI and a CI set-up to mimic the CVI based on cochlear array length and amount of active electrodes (manuscript in preparation).

However, since a minimal negative effect of these design changes on individual CI performance cannot be ruled out a priori, patients will be informed about the design changes and their potential influences. Information on how cochlear array designs might influence performance is always given to the patient when receiving a standard CI, to help the patient in making an informed decision between the different CI manufacturers. Also the patient information brochure and informed consent form will include statements on the changed cochlear array design of the CVI compared to a standard CI.

#### 5.1.2. *The processor*

To allow for stimulation of the vestibular nerves with information on head movement, the CI processor normally used with the CI implant is replaced by a research processor, the audio-motion processor (AMP). The AMP consists of two units: The audio processor, which is worn behind the ear, and the motion processor, which is worn on a cord around the neck. Both processor units are able to send information to the CVI implant using radio frequency signals via a set of coils. The internal coil is part of the implant, the external coil is connected via magnets to the internal coil and is worn on the skin behind the ear. The external coil housing also contains gyroscopes and accelerometers, which capture head motion in all directions. The external coil is connected by wire to the audio processor, which is in turn connected by wire to the motion processor. The motion processor also houses the battery.

Through the use of this combined device, both the balance and hearing organs can be stimulated simultaneously. Head motion captured by the gyroscopes and accelerometers is transferred to the motion processor where it is translated into electrical pulses. These electrical pulses are then transferred to the electrodes implanted inside each of the SCCs. This allows for the stimulation of the SCC afferent nerve branches, transferring the motion information to the brain. Using this input, the patient is able to again perceive head motion. Hearing is restored in the same way as is done with a regular CI. Sound is captured by a microphone housed in the audio processor unit, where it gets translated into electrical signals which are used to stimulate the auditory nerves inside the cochlea.

